### ***Measurement of medication adherence***

A self-developed diary card to record participants' medication adherence levels on their daily use of intranasal corticosteroid and if additional sprays are required (appendix G). The use of diaries that require participants to self-report their adherence is deemed more appropriate as it allows a more precise estimation of the number of days that the participant declares they are taking the medication. The diary card will be pre-tested prior to use. This variable will be assessed on Day 60  $\pm$ 7, Day 120  $\pm$ 7, and Day 180  $\pm$ 7.

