| Four structured questions                    | The choice of responses is either yes, not sure, or no                                                                                                                                                                                                                                                                                                                                                       | Categorical |
| Total Nasal Symptom Score (TNSS)      |                                                                                                                                                                                                                                                                                                                                                                                                              |             |
| Total Nasal Symptom Score                    | The sum of the scores of the four nasal symptoms self-rated by the patients will be presented as mean and standard deviation                                                                                                                                                                                                                                                                                 | Continuous  |
| Medication adherence                  | The mean adherence rate will be calculated by dividing the number of doses administered with intranasal steroid spray by the total number of doses the intranasal steroid spray is prescribed for. The rate will be presented in mean scores and standard deviation                                                                                                                                          | Continuous  |
| EQ-5D-5L                              |                                                                                                                                                                                                                                                                                                                                                                                                              |             |

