Their concomitant medications, if any, will be gauged in that all types of medicine that the patient is currently taking or has taken in the last 30 days will be evaluated. This includes all prescribed and over-the-counter medications. The medication dose, route, unit, frequency of administration, indication for administration, and dates of medication will be captured. Concomitant medication of study-specific interest which will be recorded during the study period includes antihistamines, corticosteroids, anticholinergics, leukotriene receptor antagonists, nasal saline, decongestants, and beta-blockers. This information will be recorded in the demography and assessment form (appendix I).

Face-to-face data collection during their physical visit to the ENT clinic will be performed at baseline and end of study follow-up (Day 180 $\pm$ 7). The post randomization follow-ups on 60 $\pm$ 7 and day 120 $\pm$ 7 will be conducted virtually (Zoom, Google Meet, Whatapps call or telephone call) or face-to-face depending on the feasibility and standard operating procedures of the outpatient ENT clinic at Hospital Raja Permaisuri Bainun during the data collection period. The reason for giving an option of virtual follow-up is to avoid adding a burden to the already extensive ENT clinic, which expects a patient load of 80–160 patients with allergic rhinitis every month. However, if the participant's clinic appointment falls on either day 60 $\pm$ 7 or day 120 $\pm$ 7, face-to-face data collection will be performed. A range of plus or minus 7 days is allowed for each scheduled time point. The data that will be collected on 60 $\pm$ 7 and day 120 $\pm$ 7 include disease severity assessment, symptom control assessment, medication adherence, and quality of life.

A checklist is created to ensure that the element of the algorithm of pharmacist management is implemented on participants assigned to the intervention group (Appendix I). Pharmacist-led educational protocol that consists of education material and structured pharmacist counselling. The educational material will be introduced to the participants assigned to the interventional group at baseline while the structured pharmacist counselling will be given to the participant in the interventional group at baseline and on 60 $\pm$ 7, 120 $\pm$ 7 and 180 $\pm$ 7. Table 3 shows a schedule of study procedures.

Table 3: Study schedule

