| Timepoint          | Screening,
D0 | Baseline,
D0 | D60 $\pm$ 7 | D120 $\pm$ 7 | D180 $\pm$ 7 |
|--------------------|------------------|-----------------|-------------|--------------|--------------|
| ENROLLMENT: |                  |                 |             |              |              |
| Eligibility screen | x                |                 |             |              |              |

|                                                      |  |   |   |   |   |
|------------------------------------------------------|--|---|---|---|---|
| Informed consent                                     |  | x |   |   |   |
| Randomization                                        |  | x |   |   |   |
| Demography & medical history                         |  | x |   |   |   |
| INTERVENTION:                                 |  |   |   |   |   |
| Educational materials                                |  | x |   |   |   |
| Pharmacist counselling                               |  | x | x | x | x |
| ASSESSMENT:                                   |  |   |   |   |   |
| Disease severity classification using ARIA guideline |  | x | x | x | x |
| Endoscopy assessment                                 |  | x |   |   | x |
| Knowledge level                                      |  | x |   | x | x |
| Symptoms control                                     |  | x | x | x | x |
| Medication adherence*                                |  |   | x | x | x |
| Quality of life                                      |  | x | x | x | x |
| Concomitant medication                               |  | x | x | x | x |

\* Patients will fill-up diary card throughout the study period on medication they have taken

Participants' knowledge levels will be evaluated by self-completing a questionnaire assessing their knowledge (appendix E). Their knowledge level will be evaluated at Day 0 (baseline), Day 120±7, and Day 180±7 during their clinic visit.

Participants' symptom control will be assessed by the researcher using TNSS (appendix F). They will be asked to reflect on their symptoms in the past 12 hours and the past 2 weeks. Symptom control will be monitored at Day 0 (baseline), Day 60 ±7, Day 120±7 and Day 180±7.

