Participants' medication adherence levels will be evaluated by asking the subject to record the diary card with details on the prescribed intranasal corticosteroid during the study (appendix G). A nasal spray administration diary card will be given to the participants on Day 0. Their adherence will be assessed during Day 60 ±7, Day 120±7 and Day 180±7. If virtual follow-up is conducted on Day 60±7 and Day 120±7, participants will be asked to take a photo of their diary card and send it to the researchers, while those without a smart phone device will be required to bring along the diary card at the end of follow-up. A phone call will

be made prior to the scheduled visit (Day 180  $\pm$ 7) to remind them to bring along the diary card. If the participants have a scheduled visit at the clinic, they will be asked to bring along the diary card.

The participants' QoL will be evaluated by self-completing EQ-5D-5L (appendix H). Their QoL will be monitored at Day 0 (baseline), Day 60 $\pm$ 7, Day 120 $\pm$ 7 and Day 180 $\pm$ 7. Two sets of paper EQ-5D-5L will be given to participants without a smart phone for them to self-complete at home during virtual follow-up on Day 60 $\pm$ 7 and Day 120 $\pm$ 7, and they are required to bring them along to the clinic (Day 180 $\pm$ 7). Participants with a smart phone will be asked to complete the questionnaire electronically (Google Form) during virtual follow-up on Day 60 $\pm$ 7 and Day 120 $\pm$ 7. If their follow-up appointment is at the same time as a scheduled clinic visit, they can complete the questionnaire on paper or online (using a Google form).

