In the determination of self-reported medication adherence, a two-way repeated measure ANOVA analysis will be used to compare the between-group differences for the mean adherence rate of number of doses of intranasal corticosteroid. It will be calculated as number of doses taken by the participants divided by the total number of doses prescribed that should be taken on regular basis. Meanwhile, the two-way repeated measures ANOVA will show the findings for the within-group comparison. A value of  $P < 0.05$  is considered statistically significant.

The participants' quality of life will be presented as a mean score and standard deviation for responses in EQ-5D-5L utility index scores. The index score will be generated by using the EQ-5D-5L index calculator for Malaysia upon getting permission from the originator (copyright holder) (Shafie et al., 2019). EQ-5D VAS will be generated in the form of a mean score and standard deviation. A two-way repeated measure ANOVA analysis will be employed to determine the mean difference between the scores of the control group and the interventional group. Within-group findings will be obtained from the analysis of two-way repeated measure ANOVA. A value of  $P < 0.05$  is considered statistically significant.

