| Night time                       |     |      |     |       |                                                                                         |     |     |
| Additional 2 Sprays              |     |      |     |       |                                                                                         |     |     |
| Another 2 Additional Sprays      |     |      |     |       |                                                                                         |     |     |
| Week 2
[ _ / _ _ to _ / _ _ ] | Mon | Tues | Wed | Thrus | Fri                                                                                     | Sat | Sun |
| Day time                         |     |      |     |       |                                                                                         |     |     |
| Night time                       |     |      |     |       |                                                                                         |     |     |
| Additional 2 Sprays              |     |      |     |       |                                                                                         |     |     |
| Another 2 Additional Sprays      |     |      |     |       |                                                                                         |     |     |
| Week 3
[ _ / _ _ to _ / _ _ ] | Mon | Tues | Wed | Thrus | Fri                                                                                     | Sat | Sun |
| Day time                         |     |      |     |       |                                                                                         |     |     |
| Night time                       |     |      |     |       |                                                                                         |     |     |
| Additional 2 Sprays              |     |      |     |       |                                                                                         |     |     |
| Another 2 Additional Sprays      |     |      |     |       |                                                                                         |     |     |
| Week 4
[ _ / _ _ to _ / _ _ ] | Mon | Tues | Wed | Thrus | Fri                                                                                     | Sat | Sun |
| Day time                         |     |      |     |       |                                                                                         |     |     |

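### The adherence diary ends at Day 168 at most, before the Day 180±7 assessment, and the adherence formula sets no reporting window and no rule for additional sprays

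*Combined protocol and SAP*

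**What the plan says.** Medication adherence is one of the four primary parameters (section 3, Primary Objective; section 5, Table 1). Within-group change in it is part of the secondary endpoint.

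- **Timing.** In section 5, Data collection: "A nasal spray administration diary card will be given to the participants on Day 0", and "Their adherence will be assessed during Day 60 ±7, Day 120±7 and Day 180±7". The same section adds: "A range of plus or minus 7 days is allowed for each scheduled time point".
- **Intended coverage.** The footnote to Table 3 says: "Patients will fill-up diary card throughout the study period on medication they have taken".
- **The card.** Appendix G prints Monday-to-Sunday grids for Weeks 1 to 24, in English and again in Malay, four weeks to a page. Each day has a day-time row, a night-time row and two further rows, the last labelled "Another 2 Additional Sprays". The section on measuring adherence says the card covers "daily use of intranasal corticosteroid and if additional sprays are required (appendix G").
- **The rate.** Statistical analysis defines it as the "number of doses taken by the participants divided by the total number of doses prescribed that should be taken on regular basis". Table 2 words it as "dividing the number of doses administered with intranasal steroid spray by the total number of doses the intranasal steroid spray is prescribed for".

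The plan does not say whether each rate covers the interval since the previous visit or all time since Day 0, which calendar days enter the denominator, how days without a diary box are scored, or whether ticks in the additional-spray rows count as doses taken.

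**The concern.** The card cannot capture the period the schedule asks of it. Twenty-four weeks is 168 days, while the last assessment may fall as late as Day 187. Depending on how the missing days are treated, the Day 180 value either omits the end of follow-up or is pulled down by days on which nothing could be ticked. In the second case the repeated-measures ANOVA would show a fall in both arms that comes from the form and not from behaviour. Because the ceiling would move with the visit date, it would also add noise unrelated to adherence.

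The additional-spray rows raise a different problem. Read literally, the numerator takes in any dose taken, while the denominator holds only doses due regularly. A participant could miss regular doses, use extra sprays and still look adherent. If extra use tracks poorer symptom control, which the intervention aims to change, this error need not be equal in the two arms.

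**Working it through.** **The plan's own figure.** The documents give no number for diary coverage or for the highest attainable rate. Their only adherence calculation is the sample size, which reproduces:

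- Pooled SD = √[(15 × 2.84² + 12 × 2.848386²)/27] = 2.84373.
- f = √(16 × 13)/29 × (93.94 − 76.62)/2.84373 = 3.02896.
- λ = f² × N × m/(1 + (m − 1)ρ) = 3.0289576² × 4 × 3/(1 + 2 × 0.5) = 55.0475. With critical F 18.5128, power is 0.9351 at N = 4, as stated.

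Enrolment is set by the EQ-5D-5L utility calculation (N = 140), so nothing below changes the sample size.

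**Diary coverage.** Inputs: 24 weekly grids (Appendix G), card issued on Day 0, last visit on Day 180 ± 7.

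- Days with a box: 24 × 7 = 168.
- Days without a box: 180 − 168 = 12 at the nominal visit; 173 − 168 = 5 and 187 − 168 = 19 at the window limits.
- The grids run Monday to Sunday. A late-week start can lose up to 6 boxes in Week 1, giving 168 − 6 = 162 days.

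**Highest rate for a fully adherent patient at the last assessment.** The capped rows assume that the denominator runs to the visit, boxless days count as not taken, no further page is issued and extra sprays are not counted.

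| Reading | Formula | Nominal | Last visit Day 173 to 187 |
|---|---|---|---|
| Per interval, from Day 120 | (168 − 120)/(visit − 120) | 48/60 = 80.0% | 48/53 = 90.6% to 48/67 = 71.6% |
| Cumulative, from Day 0 | 168/visit | 168/180 = 93.3% | 168/173 = 97.1% to 168/187 = 89.8% |
| Denominator ends with the diary | same days in both parts | 100% | 100% |

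If the Day 120 visit also moves in its window, the interval range widens to (168 − 127)/(187 − 127) = 41/60 = 68.3% and (168 − 113)/(173 − 113) = 55/60 = 91.7%.

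**Effect on the planned difference.** The planning means differ by 93.94 − 76.62 = 17.32 points.

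- Per interval: 0.8 × 17.32 = 13.86 at Day 180. Averaged over three assessments, 17.32 × (1 + 1 + 0.8)/3 = 16.17.
- Cumulative: 17.32 × 168/180 = 16.17 at Day 180. Averaged, 17.32 × (1 + 1 + 168/180)/3 = 16.94.

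**Additional sprays.** For illustration, assume 14 regular doses a week and one dose per extra tick; the documents fix neither and give no frequency of extra use. With 60% regular use (0.6 × 14 = 8.4 doses):

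- 2 extra ticks a week: (8.4 + 2)/14 = 74.3%.
- 7 extra ticks a week: (8.4 + 7)/14 = 110%.

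**Grids needed.** 27 × 7 = 189 days reaches Day 187 after a start at or near the beginning of the grid, but after a Sunday start leaves 189 − 6 = 183. 28 × 7 − 6 = 190 always reaches it.

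**The case against.** A reader might infer that last-interval adherence is simply capped near 80%. The documents do not support that as a fact. It needs a per-interval rate, a denominator running to the visit, boxless days scored as missed, no extra page issued and additional sprays left out. The plan settles none of these. A cumulative rate gives about 93%, and a denominator confined to diary days gives no cap. The two problems also cannot both act at full strength: if extra sprays count, 80% is not a ceiling. On twice-daily use, half an extra tick per day gives 48 × 2.5/120 = 100%.

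The additional-spray reading is open too. The card keeps those rows separate, so they can be left out. The numerator can reasonably be read as regular doses only, and Table 2 puts no limit to regular doses on the denominator.

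The effect may also be modest. Both arms use the same card and only one of three assessments is affected. If every rate were multiplied by 0.8, the SD would shrink in step and the standardised difference at that visit would not change. Power is not at risk on the plan's inputs.

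All of this stands, and it limits the claim about size. It does not remove the mismatch between a 168-day card and a final visit on Day 173 to 187, nor the lack of any rule for the window or the extra rows. Days that were never recorded cannot be reliably recovered later.

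**Conclusion.** The point holds in a bounded form. It is certain that the card in both languages ends 5 to 19 days before the last adherence assessment (more after a mid-week start), against the protocol's own instruction to keep the diary for the whole study. It is conditional that a fully adherent patient's Day 180 rate is limited to about 80% per interval (72% to 91%) or about 93% cumulatively (90% to 97%). That requires the denominator to run to the visit and unrecorded days to count as not taken. The result would then be a false fall in both arms, bearing chiefly on the within-group secondary endpoint, and a somewhat smaller between-arm difference in points.

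It is also certain that the formula in Statistical analysis, as worded, neither excludes nor caps additional sprays. A reader might go on to infer that this reverses the arm comparison. Nothing in the documents shows that: they give no rate of extra use in either arm, so size and direction are unknown. The sample size is unaffected. As the variable is a primary parameter and the data must be collected prospectively, the rule should be fixed before the data are seen.

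**What to change.** 1. Extend the card to 28 weekly grids. Twenty-seven suffice only if Week 1 starts on Day 0 or the participant starts early in the printed week. Otherwise, end numerator and denominator on the same last diary day and say that the Day 180 value stops there.
2. State whether each rate is per interval or cumulative, and how blank or boxless days are handled.
3. Define the rate as regular day-time and night-time doses ticked over regular doses prescribed for the same dates, capped at 100%. Use the same wording in Table 2 and in Statistical analysis.
4. Report additional sprays as a separate variable.

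Cost: at four weeks to a page, one more diary page per language (seven in place of six), and a few sentences in the analysis section.

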## **Statistical analysis**

An intention-to-treat analysis will be used to include all of the patients who were assigned to each group after randomization. The data analysis will be done using SPSS version 20.0. Descriptive data will be expressed as mean and standard deviation (SD) if the data is normally distributed, or median and interquartile range (IQR) if the data is not normally distributed. Categorical data will be presented in frequency and percentage.

To determine the knowledge level, The “yes” answer will be given a score of two, the “no” answer will be given a zero score, and “not sure” will be given a score of one (Retinasekharan et al., 2021). The outcome will be presented in mean score and standard deviation for each group. Each question will be analysed separately. The knowledge levels will be assessed at baseline, Day 120 $\pm$ 7 and on Day 180  $\pm$ 7. Between-group comparisons will be analysed using Two-way repeated measure ANOVA to compare mean score different between two groups. Meanwhile, the two-way repeated measures ANOVA will show the findings for the within-group comparison. A P-value of < 0.05 will be considered statistically significant.

The Total Nasal Symptom Score (TNSS) is the sum of scores for each of nasal congestion, sneezing, nasal itching, and rhinorrhoea at each time point, using a four-point scale (0–3), where 0 indicates no symptoms, a score of 1 for mild symptoms that are easily tolerated, a

score of 2 for awareness of symptoms that are bothersome but tolerable, and a score of 3 is reserved for severe symptoms that are hard to tolerate and interfere with daily activity. A higher score indicates the more severe the symptoms are, and the main outcome of TNSS will be generated as a mean and standard deviation. A mean score will be calculated separately for the past 12 hours and past 2 week. A two-way repeated measure ANOVA analysis will be employed to determine the mean difference between the scores of the control group and the interventional group in order to determine the overall effectiveness of the intervention. Within-group comparisons will be shown as part of the outcome of the two-way repeated measures ANOVA. A value of  $P < 0.05$  is considered statistically.

In the determination of self-reported medication adherence, a two-way repeated measure ANOVA analysis will be used to compare the between-group differences for the mean adherence rate of number of doses of intranasal corticosteroid. It will be calculated as number of doses taken by the participants divided by the total number of doses prescribed that should be taken on regular basis. Meanwhile, the two-way repeated measures ANOVA will show the findings for the within-group comparison. A value of  $P < 0.05$  is considered statistically significant.

The participants' quality of life will be presented as a mean score and standard deviation for responses in EQ-5D-5L utility index scores. The index score will be generated by using the EQ-5D-5L index calculator for Malaysia upon getting permission from the originator (copyright holder) (Shafie et al., 2019). EQ-5D VAS will be generated in the form of a mean score and standard deviation. A two-way repeated measure ANOVA analysis will be employed to determine the mean difference between the scores of the control group and the interventional group. Within-group findings will be obtained from the analysis of two-way repeated measure ANOVA. A value of  $P < 0.05$  is considered statistically significant.

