**4 ETHICS & REGULATORY CONSIDERATIONS**

**Ethical conduct of the study**

Ethical approval will be obtained from the Medical Research and Ethics Committee (MREC) through NMRR before the study is conducted.

The study will be conducted in compliance with the protocol and standard operating procedures. These are designed to ensure adherence to the ethical principles that have their origin in the "World Medical Association Declaration of Helsinki", "Malaysian Guidelines for Good Clinical Practice" and applicable regulatory Requirements.

All study data will be stored for 3 years after the study findings are published and then destroyed. All data will be kept under lock and key in the office cabinet and only accessible by the researchers. Participants in this study will not be given access nor informed of the findings' outcome. The participants will be informed with the new information if it becomes available during the study. The patient educational material will be shared with all the participants, including the control group, at the end of the study.

Participants can choose to withdraw at any time. The physician or investigator may withdraw participants if there is an associated risk with the participants' continuing participation in this study. All withdrawn participants will be reminded to continue receiving their standard medical care at the ENT clinic at Hospital Raja Permaisuri Bainun. Withdrawn participants will not be replaced. The data collected from the withdrawn participants will be included in the analysis.

The participants will not be informed individually about the study findings; however, the patient education material will be shared with all the participant (including the control group)

at the end of this study. The control group participants will be subjected to structured pharmacist counselling at the end of study, right after their data are collected. All the information obtained from this study will be kept confidential and only summarized data, without unique identifier, will be presented in reports or publications upon getting permission from the Director General of Health, Ministry of Health Malaysia.

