#### **Results of the G-power calculator:**

F tests - ANOVA: Repeated measures, within factors

Analysis: A priori: Compute required sample size

Input: Effect size  $f$  = 0.1005038

$\alpha$  err prob = 0.05

Power ( $1-\beta$  err prob) = 0.80

Number of groups = 2

Number of measurements = 4

Corr among rep measures = 0.5

Nonsphericity correction  $\epsilon$  = 1

Output: Noncentrality parameter  $\lambda$  = 11.1515193

Critical F = 2.6267747

Numerator df = 3.0000000

Denominator df = 408

Total sample size = 138

Actual power = 0.8056554

Therefore, 69 samples are required for each group

The sample size selected will be 70 participants for each group after considering the highest sample size calculated for each specific objective. By estimating the predicted drop-out rate of 10%, 77 participants for each group will be required for this phase. A total of 154 participants will be recruited for this study.

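### Intention-to-treat is promised, but the only named method, repeated-measures ANOVA with no missing-data rule, analyses each primary outcome on its own complete-case subset

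*Combined protocol and SAP*

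**What the plan says.** On who is analysed, the Statistical analysis section says: "An intention-to-treat analysis will be used to include all of the patients who were assigned to each group after randomization". Under Ethical conduct of the study, on withdrawals: "The data collected from the withdrawn participants will be included in the analysis".

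On method, the same technique is named for each primary outcome:
- Knowledge: "Between-group comparisons will be analysed using Two-way repeated measure ANOVA to compare mean score different between two groups".
- TNSS and EQ-5D-5L: "A two-way repeated measure ANOVA analysis will be employed to determine the mean difference between the scores of the control group and the interventional group".
- Adherence: "a two-way repeated measure ANOVA analysis will be used to compare the between-group differences for the mean adherence rate".
- Within-group results for quality of life: "Within-group findings will be obtained from the analysis of two-way repeated measure ANOVA". The other outcomes are handled in the same way.

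On software: "The data analysis will be done using SPSS version 20.0".

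On expected loss, the Sample size section says: "By estimating the predicted drop-out rate of 10%, 77 participants for each group will be required for this phase". Elsewhere the plan allows withdrawal at any time without replacement, ends follow-up on pregnancy, and defines loss to follow-up. Participants without a smartphone return their Day 60 and Day 120 EQ-5D-5L forms and diary at the Day 180 visit.

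No section gives an imputation method, a likelihood-based model, a missing-data assumption or a missing-data sensitivity analysis.

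**The concern.** Repeated-measures ANOVA needs a value at every time point that enters the model. In SPSS the repeated-measures procedure removes a participant with any gap from that analysis. With nothing in the plan to fill or model the gaps, the analysis set for each outcome is its completers, not everyone randomised. Visits already collected from a withdrawn participant are left out of the test.

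The deletion works outcome by outcome. TNSS and EQ-5D-5L use baseline and Days 60, 120 and 180. Adherence uses Days 60, 120 and 180. Knowledge uses baseline and Days 120 and 180 (Table 3). A missed Day 60 therefore affects TNSS, EQ-5D-5L and adherence but not knowledge, and the four primary outcomes can rest on different subsets.

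Participants know whether they are receiving repeated counselling, so the reasons for leaving can differ by arm. If poor responders leave one arm more often, the remaining groups are no longer comparable and the estimate is biased. Lost power is a smaller matter. Leaving the rule open also lets deletion, carrying values forward or imputation be chosen after results are seen.

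**Working it through.** **Inputs from the plan.** EQ-5D utility drives the sample size: means 0.909 and 0.943, pooled SD 0.090139, 4 measurements, correlation 0.5, alpha 0.05, 140 required, 154 randomised, 10% dropout.

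**Assumed.** The documents give no visit-level missing rate. I take 3%, 5% and 10% per follow-up, independent across the three follow-ups.

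**1. Reproduce the plan's figure.**
- f = (0.943 − 0.909) / 2 / 0.090139 = 0.1886.
- λ = N × f² × m / (1 + (m − 1)ρ) = 140 × 0.1885976² × 4/2.5 = 7.967.
- The non-central F on 1 and 138 df gives power 0.8004. Both match the plan.

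**2. Complete cases and power for EQ-5D utility.** Completers = 154 × (1 − p)³, multiplied by 0.9 where the 10% dropout is added. Power comes from the same formula.

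| Loss | Completers of 154 | Power |
|---|---|---|
| None | 154 | 0.837 |
| 10% dropout only | 138.6 | 0.796 |
| 3% per visit only | 140.6 | 0.80 |
| 5% per visit only | 132.0 | 0.78 |
| 10% per visit only | 112.3 | 0.71 |
| 10% dropout and 3% per visit | 126.5 | 0.76 |
| 10% dropout and 5% per visit | 118.8 | 0.73 |
| 10% dropout and 10% per visit | 101.0 | 0.66 |

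With no other loss, completers fall below 140 when the rate per visit exceeds 1 − (140/154)^(1/3) = 3.1%. Knowledge loses fewer participants because it has only two follow-ups: at 5% per visit, 154 × 0.95² = 139.0.

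**3. Bias with no true effect.** Suppose scores have SD 1 and correlation 0.5 between all visits, and the worst fraction p at Day 60 leaves an arm afterwards. The Day 60 mean of those who stay improves by φ(z)/(1 − p), where z cuts off the worst p. Averaged over four visits, the shift is multiplied by (1 + 3 × 0.5)/4 = 0.625.
- 15% v 5%: 0.2743 − 0.1086 = 0.1657, and 0.1657 × 0.625 = 0.10 SD.
- 12% v 8%: 0.2273 − 0.1616 = 0.0657, and 0.0657 × 0.625 = 0.04 SD.
- 10% v 10% under the same rule: 0.

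The planned utility effect is 0.034/0.090139 = 0.38 SD, so these artefacts are about 27% and 11% of it.

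**4. Softer mechanisms, by simulation.**
- If leaving is only made more likely by a poor Day 60 score (log-odds 0.5 or 1.0 per SD), 15% v 5% dropout gives about 0.03 or 0.05 SD.
- Equal 10% dropout in both arms does not guarantee safety. When it depended on the Day 60 score differently by arm, the spurious difference was 0.06 to 0.11 SD.

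In all these cases dropout depends on an observed score. This is missing-at-random, which a likelihood-based model using all observed visits can handle.

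**The case against.** The strongest reply is that the plan nowhere says incomplete participants will be deleted, names no specific SPSS procedure, and states the opposite intention twice. That is true: the deletion is inferred from the method. But the intention has no mechanism behind it. An analyst who ran the named ANOVA would get complete-case results, and one who did anything else would be choosing outside the plan.

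Two stronger readings are tempting, and the documents support neither.
- A reader might infer that someone who misses Day 60 contributes nothing. Knowledge is not measured at Day 60, so that participant stays in one primary outcome, and can also appear in the descriptive summaries.
- A reader might infer that missed visits will remove more than the 10% allowance. No visit-level rate is given. At 3% per visit alone the loss is 8.7%, and 140.6 participants remain. The plan does not say whether its 10% already covers missed visits, so adding the two is a scenario rather than a forecast.

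The plan also works to limit missing data: virtual, telephone or face-to-face contact at Days 60 and 120, a reminder call before Day 180, and repeated calls and a letter before declaring loss to follow-up. These may keep the rates low. They do not say what happens to the gaps that remain.

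The 0.10 SD bias needs exactly the worst scorers to leave at 15% v 5%; milder assumptions give less. It shows a risk, not an expected result.

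**Conclusion.** The point holds. The promised analysis set and the named method do not agree for any of the four primary outcomes, and no missing-data method reconciles them. That conclusion needs no assumed rate, only that some visits are missed, which the plan's own 10% dropout allows for.

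The size is conditional. Bias is about 0.04 to 0.10 SD under the worst-scorer mechanisms shown, less under softer ones, and zero if dropout follows the same rule at the same rate in both arms. It would be wrong to say that the protection of randomisation is certainly lost. Power is a weak argument alone: 0.796 at 10% dropout is essentially the target, and 0.76 to 0.66 rests on assumed missed visits on top of dropout.

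It should be settled before data are seen, because it governs every primary outcome.

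**What to change.** In the Statistical analysis section:
- Make the primary analysis a linear mixed model for repeated measures (SPSS MIXED, all observed visits, unstructured covariance) for both TNSS recall periods, EQ-5D utility, EQ VAS, adherence and each 0–2 knowledge item score.
- Use baseline as a covariate, except for adherence, which has no baseline measurement. Alternatively, keep baseline as a repeated outcome where it exists, so that participants with only a baseline value also contribute.
- State which between-group contrast is primary. The sample size for utility used the average over four measurements. If baseline becomes a covariate the contrast changes, and the calculation should be checked against it.
- Report, by arm and outcome, how many randomised participants have no usable data. With baseline as a covariate, the model still omits anyone without a follow-up value, so the statement that everyone randomised is included needs matching wording.
- Add one reference-based or delta-adjusted sensitivity analysis for data not missing at random.
- Keep repeated-measures ANOVA, if wanted, only as a labelled complete-case analysis.

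The cost is SAP wording, the sample-size check where the contrast changes, and slightly more analysis work. It needs no new software and no new data collection. The downside is reliance on missing-at-random, which the sensitivity analysis is there to probe.
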